#### Inclusion/exclusion criteria

Screening to determine eligibility (with the exception of HLA haplotyping) will be completed within 45 days of study entry.

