##### --Patient Characteristics--

1. Age: 18 and over, able to give written informed consent. Individuals unable to provide informed consent must have consent provided by the legal guardian, or person designated by the subject to give consent on his behalf.

2. Performance status: Karnofsky 70-100%

3. Life expectancy: At least 1 year

4. Hematopoietic: obtained twice, once within 45 days prior to study entry, and again within 72 hours of study entry.

WBC greater than 3,800

Absolute neutrophils greater than 1,500

Absolute lymphocytes greater than 500

Platelets greater than 120,000

Hb at least 10 g/dl

5. Hepatic:

Bilirubin less than 2.0 mg/dl OR

SGOT less than 2 x ULN

6. Renal:

Creatinine no greater than 2.0 mg/dl OR

Creatinine clearance at least 40 ml/min

7. Rheumatologic:

ANA no greater than upper limit of normal, or ANA abnormal in absence of clinical signs of autoimmunity.

Rheumatoid factor (RF) no greater than upper limit of normal, or RF abnormal in absence of clinical signs of autoimmunity.

Anti-ds DNA no greater than upper limit of normal, or anti ds DNA abnormal in absence of clinical signs of autoimmunity.

1. Immunologic:

Influenza serology (assessment made at time of screening).

Assessment of DTH response to a tandard anergy panel (to include candida, trichophyton and tetanus) or to a Multitest CMI (a disposable kit for DTH testing with standardized preloaded antigens).

1. Cardiovascular:

No NYHA class III/IV status

No active angina, clinically significant cardiac arrythmia, recent (6 months) myocardial infarction

1. Pulmonary:

No severe debilitating pulmonary disease

1. Endocrine:

TSH, T3, and T4 no greater than upper limit of normal

1. Radiographic:

Baseline bone scan

Baseline CT or MRI of abdomen and pelvis

1. Other:

No active infection requiring antibiotics

No active pain requiring chronic opioid analgesics.

Not HIV, hepatitis B or hepatitis C virus positive; anti-HIV, HbsAg and Hep C antibody negative

No history of hypersensitivity to vaccine components

No serious uncontrolled medical illness

No currently active second malignancy other than non-melanoma skin cancer (note: a patient is NOT considered to have currently active malignancy if they have completed therapy and are now considered by their physician to be at less than 30% risk for relapse)

No history of total lymph node irradiation

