##### Definitions for Schedule of Events

###### Screening. Screening will generally be completed within 45 days prior to study entry.

Medical History: The Principal Investigator or his designee will perform a thorough medical history.

Complete Physical Examination: The Principal Investigator or his designee will perform a complete physical exam at the indicated times.

Tests listed below will be conducted on samples collected and analyzed by standard procedures.

If any laboratory result is outside the reference range and is considered to be clinically relevant by the Investigator, the test will be repeated at appropriate time intervals until it returns to baseline or becomes a clinically insignificant finding.

Complete Blood Count: including differential white blood cell count, absolute neutrophil count, hemoglobin and platelet count.

Hematologic Tests: PT/PTT.

Blood Chemistries: Including total electrolytes (Na, K, Cl and bicarbonate, glucose, serum BUN and creatinine, alkaline phosphatase, and albumin.

Liver Function Tests: AST, ALT and total bilirubin.

Urinalysis: Including microscopic analysis.

Viral screens: HCV antibodies, Hepatitis B surface antigen, HIV antibodies, Influenza serology.

Rheumatologic screens: ANA, RF, dsDNA.

Thyroid screens: TSH, T3, T4.

HLA haplotype: complete HLA haplotype is obtained as part of the patient database, but is not used as a clinical screening parameter. Results of HLA haplotyping do not need to be available prior to leukapheresis at week 0.

Immunologic: DTH testing to standard anergy panel, including candida, tryichophyton and tetanus.

EKG

Radiologic Tests will be performed at Memorial Sloan-Kettering Cancer Center (preferably) or New York Weill Medical College. All tests will be read by a professional radiologist and compared with prior studies whenever these are available.

Chest X-Ray: Standard PA and lateral chest X-Ray, to be completed during screening, and, for follow-up imaging during the study, within 10 days of the dates indicated in the Schedule of Events.

Bone Scan: To be completed during screening, and, for follow-up imaging during the study, within 10 days of the dates indicated in the Schedule of Events.

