##### Activity

Activity of vaccination will be measure by monitoring both clinical and immunologic parameters. The primary clinical parameter of activity will be PSA measurement. Secondary clinical parameters include monitoring of measurable disease, assessed by chest X-Ray, bone scan and CT scan/MRI scans.

PSA will be measured in the MSKCC laboratory and serially monitored starting at the screening visit, Day 0, Week 3, 4, 5, 7, 9, 13, and 17, (and possibly 29) for participants in Arm 1 and on screening visit, Week 3, 4, 5, 6, 7, 9, 11, 12, 13, 15, 17, 21, and 25, (and possibly 37) for participants in Arm 2.

Complete response (CR): PSA < 4.0 ng/ml for 3 successive evaluations at least two weeks apart.

Partial Response (PR): Decrease in PSA value by > 50% (without normalization) for three successive evaluations at least two weeks apart.

Stabilization (SD): Patients who do not meet the criteria for PR or PD for at least 90 days on study (post vaccine; week 1 (Arm 1) or week 10 (Arm 2)).

Progression (PD): Three consecutive increase in PSA from baseline or nadir, each measurement at least two weeks apart.

Time to PSA Progression: The first PSA rise after the nadir PSA that is confirmed by two consecutive PSA at least two weeks or more apart.

Measurable disease

Patients will be evaluated at baseline, and at 5 weeks and 17 weeks after completion of therapy. Response and progression of measurable disease will be evaluated by bone scan and soft-tissue CT scan, using criteria proposed by the Response Evaluation Criteria in Solid Tumors (RECIST) Committee (Therasse et al., 2000). Changes in only the largest diameter (uni-dimensional measurement) of the tumor lesions are used in the RECIST criteria. Note: Lesions are either measurable or non-measurable using the criteria provided below.

Measurable disease: Defined as lesions that can be accurately measured in at least one dimension (longest diameter to be recorded) as >20 mm with conventional techniques (PET, CT, MRI, x-ray) or as >10 mm with spiral CT scan.

Non-measurable disease: All other lesions, including small lesions, are considered non-measurable disease. Bone lesions, leptomeningeal disease, ascites, plueral/pericardial effusions, lymphangitic disease, inflammatory disease are all non-measurable.

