Target lesions: All measurable lesions up to a maximum of five per organ and 10 in total representative of all involved organs should be identified as target lesions and recorded and measured at baseline. Target lesions should be selected on the basis of their size (lesions with the longest diameter) and their suitability for accurate repeated measurements (either by imaging techniques or clinically). A sum of the longest diameter (LD) for all target lesions will be calculated and reported as the baseline sum LD, which will serve as a reference by which to characterize tumor response.

Non-target lesions: All other lesions should be identified as non-target lesions and should also be recorded at baseline. Non-target lesions include measurable lesions that exceed the maximum numbers per organ or total of all involved organs as well as non-measurable lesions. Measurements of these lesions are not required, but the presence or absence of each should be noted throughout follow-up.

Guidelines for evaluation of measurable disease: All measurements should be taken and recorded in metric notation using a ruler or calipers. All baseline evaluations should be performed as closely as possible to the beginning of treatment and never more than 4 weeks before the beginning of the treatment. Tumor lesions that are situated in a previously irradiated area are not considered measurable. The same method of assessment and the same technique should be used to characterize each identified and reported lesion at baseline and during follow-up. Imaging-based evaluation is preferred to evaluation by clinical examination when both methods have been used to assess the antitumor effect of a treatment.

Radionuclide bone scan

Subjectivity in interpreting serial changes in radionuclide bone scan is well recognized. Thus the primary outcome will be whether the scan is stable or improved, vs. worse or progression. Changes in intensity will not be used as an outcome measure.

Stable or improved: Requires that no new lesions appear, or that new pain has not developed in an area that was previously visualized.

Progression (Non-response): New areas of focal uptake.

Time to Progression: Time to progression will be defined as the time from the first day of treatment with vaccine until the date PD or death is first reported. Patients who die without a reported prior progression will be considered to have progressed on the day of their death.

Chest x-ray

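### The 45-day screening window conflicts with the 4-week limit on baseline imaging, and in Arm 2 the only baseline scan named in the text precedes the placebo phase although time to progression starts at first vaccine

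*Combined protocol and SAP*

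**What the plan says.** All references are to the combined protocol and SAP.

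- **Screening window.** Inclusion/exclusion criteria: "Screening to determine eligibility (with the exception of HLA haplotyping) will be completed within 45 days of study entry". Definitions for Schedule of Events, Screening: "Screening will generally be completed within 45 days prior to study entry".
- **Baseline imaging is a screening item.** The Screening definitions state "Bone Scan: To be completed during screening". The Radiographic entry under Patient Characteristics lists "Baseline CT or MRI of abdomen and pelvis".
- **Entry to first injection.** On-study evaluations, Entry (Week 0): entry is the day of leukapheresis, 8-9 days before the first immunization at week 1.
- **Age limit on the baseline.** Activity, guidelines for evaluation of measurable disease: "never more than 4 weeks before the beginning of the treatment".
- **Arm 2 timing.** Dosing Plan: placebo at weeks 1, 3, 5 and 7; first dendritic-cell vaccine at week 9.
- **Imaging visits.** Activity, measurable disease: "Patients will be evaluated at baseline, and at 5 weeks and 17 weeks after completion of therapy". Table 2, which sets the follow-up imaging dates, is not in the supplied text.
- **Clock.** Activity, Time to Progression: "the time from the first day of treatment with vaccine until the date PD or death is first reported". The baseline sum of longest diameters is the reference for response, and any new focus of uptake on bone scan counts as progression.

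**The concern.** Two things do not fit together.

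First, a site that works from the screening window alone can obtain a baseline scan well outside the 4-week limit. The text does not tell sites which part of the window satisfies both rules.

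Second, in Arm 2 the baseline and the clock sit on opposite sides of the placebo phase. The reference scan is taken before week 1 and time starts at week 9. On the text alone, the next scan comes 5 weeks after the last vaccination. A bone lesion that appears during placebo, or soft-tissue disease that grows then, would first be seen after vaccination and dated on a vaccine clock. PSA does not share the problem, because it is measured repeatedly during the placebo weeks.

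At stake is the interpretation of imaging response and time to progression for the Arm 2 vaccine period. Any error runs against the vaccine.

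**Working it through.** The 4-week limit (28 days) is a rule, not a derived figure, so there is no plan calculation to reproduce. The check is calendar arithmetic.

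**Inputs.** Scan to entry: 0-45 days (screening window). Entry to week 1: 8-9 days (Entry definition). Week 1 to week 9: 7 × 8 = 56 days (Dosing Plan). Injection window: ±3 days, except for the first injection (On-study evaluations). Last vaccine: week 7 in Arm 1, week 15 in Arm 2.

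**1. Scan to first study injection, both arms**
- Shortest 0 + 8 = 8 days; longest 45 + 9 = 54 days.
- Oldest scan that meets 28 days: 28 − 9 = 19 days before entry, or 28 − 8 = 20 days if the injection is on day 8.
- 54 is not a hard cap. The Screening definitions say the 45 days apply only generally, and leukapheresis may be repeated.

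**2. Scan to first vaccine, Arm 2**
- Nominal: 0 + 8 + 56 = 64 to 45 + 9 + 56 = 110 days.
- Through the week 8 leukapheresis (nominal day 56): 0 + 56 + 8 = 64 to 45 + 56 + 9 = 110 days, the same range.
- If the ±3-day window applies to the week 9 visit: 64 − 3 = 61 to 110 + 3 = 113 days. This depends on whether the exempt first injection in Arm 2 is the week 1 placebo (window applies at week 9) or the week 9 vaccine (it does not).
- Even the smallest value exceeds the limit by 61 − 28 = 33 days.

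**3. First follow-up scan in the text**
- Arm 1: week 7 + 5 = week 12. Arm 2: week 15 + 5 = week 20.
- The second scan falls at week 7 + 17 = 24 and week 15 + 17 = 32. Routine follow-up under Duration ends at weeks 17 and 25.

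**4. How many Arm 2 patients might be affected**

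The documents give no rate for this population. The nearest figure, in Background, is a nearly 50% chance of evident metastatic disease within 3 years for patients with a high-grade tumor and a PSA rise within 2 years. Reading that as a 36-month median (about 1,096 days) with exponential times is an assumption. A 12-month median (about 365 days) is a second assumption, added to show the range. The probability of a new lesion within t days is 1 − 2^(−t/median).

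| Interval in Arm 2 | 36-month median | 12-month median |
|---|---|---|
| Scan to first vaccine, 64 days | 4.0% (0.5 of 12) | 11% (1.4 of 12) |
| Scan to first vaccine, 110 days | 6.7% (0.8 of 12) | 19% (2.3 of 12) |
| Placebo period alone, 56 days | 3.5% (0.4 of 12) | 10% (1.2 of 12) |

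The last row is the excess over Arm 1. The rest of each interval is screening and lead-in time that Arm 1 shares.

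**The case against.** The strongest reply is that Table 2 cannot be seen. The protocol says it includes all study evaluations, and the follow-up imaging dates are deferred to it. A rescan near week 8 would remove the Arm 2 problem. This stands as a limit: the imaging sentence under Activity names no such scan, but it does not exclude one.

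Second, Arm 1 is not forced into a breach. The 4-week rule is the stricter and more specific one, and a site that follows it can satisfy both. That also stands. The defect is that the 45-day window permits the older scan without warning.

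Third, if treatment begins with the first study injection, placebo included, Arm 2 can meet the 4 weeks at week 1. True, and the plan does not define the term. But the time-to-progression clock explicitly starts at vaccine, so its mismatch with the baseline remains on either meaning.

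Fourth, the 4-week limit sits under measurable disease, and bone lesions are classed as non-measurable. The sentence nevertheless covers baseline evaluations generally. The clock mismatch applies to bone scans whether or not the limit does.

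A reader might infer more: that every Arm 2 patient breaks the rule, or that the vaccine will look worse in Arm 2 when the arms are compared or pooled. The documents do not support either. The first depends on Table 2 and on an undefined term. For the second, no pooled or between-arm imaging analysis is planned; the analysis sections cover immunogenicity, PSA and adverse events.

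**Conclusion.** The conflict between the 45-day window and the 4-week limit is certain and needs only the plan's own dates: up to 54 days is permitted against 28. The Arm 2 mismatch is also real on the text: the screening scan is 64-110 days old (61-113 with the visit window) when the vaccine clock starts. That progression arising on placebo is then scored as progression on vaccine is conditional on Table 2 containing no pre-vaccine rescan.

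The consequence is limited. Imaging is a secondary clinical parameter with no planned test, so the affected result is descriptive. The primary comparison is made before cross-over and uses PSA, which is unaffected. Under the stated assumptions, roughly 0.5-0.8 of 12 Arm 2 patients (36-month median) to 1.4-2.3 of 12 (12-month median) would have a new lesion between scan and first vaccine. The medians are illustrations, not trial data.

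**What to change.** 1. In Inclusion/exclusion criteria and in the Screening definitions, require the baseline bone scan and CT/MRI within 19 days before entry. The gap to first injection is then at most 19 + 9 = 28 days in both arms.
2. Under Activity, define when treatment begins in Arm 2. Change 1 does not cure the vaccine period there: the nominal gap to week 9 would still be 64 to 19 + 9 + 56 = 84 days. So do not report Arm 2 vaccine-period imaging response or time to progression from the screening scan unless a scan within 4 weeks before the week 9 vaccine exists.
3. Reconcile the imaging sentence under Activity with Table 2, and state whether there is such a scan.
4. If time to progression is instead measured from the first study injection in both arms, do not compare the arms on it. The first follow-up scan falls at about week 12 in Arm 1 and week 20 in Arm 2, so progression could be detected about 8 weeks earlier in Arm 1.

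Moving the first follow-up scan to week 8 or 9 is not recommended. The remaining scan in Arm 2 would fall at about week 32, after routine follow-up ends at week 25, so there might be no routine post-vaccine scan to compare with the new baseline.

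Cost: slightly tighter scheduling of scans already required, no added scans, and possibly no Arm 2 vaccine-period imaging result.

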### Study Design

Phase I/II prospective randomized, single-blinded, placebo-controlled trial with 2 arms describing the toxicity and activity of immunization with DC-LNCaP. Study participants in Arm 2, but not the investigator, study personnel, or those study participants in Arm 1 will be blinded with respect to up-front treatment (vaccine or placebo). At week 8, all patients will be made aware of which treatment arm they are in.

Arm 1. Subcutaneous injection of *ex vivo* generated autologous dendritic cells pulsed with apoptotic LNCaP cells, pulsed with apoptotic LNCaP-M1 cells (control apoptotic cells) and pulsed with KLH (control antigen). In addition, subcutaneous injection of either saline or vaccine vehicle only (5% DMSO in normal saline ).

Arm 2. Subcutaneous injection of either saline or vaccine vehicle only (5% DMSO in normal saline ), followed by cross-over to Arm 1 design.

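### The two bone scan categories are not complementary: with the written 'or' one kind of patient meets both, and read as 'and' another kind meets neither

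*Combined protocol and SAP*

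**What the plan says.** In the Activity part of Outcome Parameters (protocol section (6)i.h), PSA is the primary clinical parameter. The bone scan ranks below it: "Secondary clinical parameters include monitoring of measurable disease, assessed by chest X-Ray, bone scan and CT scan/MRI scans".

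The paragraph on the radionuclide bone scan first concedes that serial scans are read subjectively. It responds by reducing the result to two outcomes: "Thus the primary outcome will be whether the scan is stable or improved, vs. worse or progression". It also removes one possible source of change: "Changes in intensity will not be used as an outcome measure".

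Two definitions follow. For *stable or improved*: "Requires that no new lesions appear, or that new pain has not developed in an area that was previously visualized". For the opposite side: "Progression (Non-response): New areas of focal uptake". The word *worse*, which appears in the two-way outcome, gets no definition.

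Time to progression comes directly after these definitions and ends at the first report of either event: "Time to progression will be defined as the time from the first day of treatment with vaccine until the date PD or death is first".

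**The concern.** A two-way outcome needs two definitions that exclude each other and together cover every patient. These do not. The favourable side depends on lesions and pain, joined by 'or'. The unfavourable side depends on uptake alone. Since pain enters only one side, the result for some patients depends on how the reader interprets a conjunction.

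Pain also fits poorly with the paragraph's purpose. The two-way outcome was chosen to limit subjectivity in reading scans, yet pain is not visible on a scan and has to come from the patient's history.

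What is at stake is limited: how a secondary activity parameter is reported. With no rule fixed in advance, the choice between the two readings would be made once the affected scans are in hand. If bone scan progression feeds the time-to-progression definition, an event date could change as well.

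**Working it through.** The plan gives no figure to reproduce. The check lists every combination and applies the definitions to each.

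**Inputs**, all from the radionuclide bone scan paragraph in section (6)i.h:
- L = a new lesion appears (yes/no). 'New lesion' and 'new focal uptake' are taken as the same finding, which is the natural reading for a bone scan.
- P = new pain develops at a site already seen on scan (yes/no).
- Progression = L.
- Stable, as written = (not L) or (not P).
- Stable, if 'or' is meant as 'and' = (not L) and (not P).

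**Result**

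| New lesion | New pain | Written 'or' | Read as 'and' |
| --- | --- | --- | --- |
| No | No | Stable | Stable |
| No | Yes | Stable | **Neither** |
| Yes | No | **Both** | Progression |
| Yes | Yes | Progression | Progression |

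With 'or', the two categories cover all four combinations but overlap in one. With 'and', they do not overlap but leave one combination uncovered. Neither reading divides patients cleanly.

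**Does another part of the plan settle it?**
- *Worse* could have held the pain-only patient, but it is undefined, and the only definition on that side is new uptake.
- Change in intensity is excluded, so it cannot decide the matter.
- The Biostatistical analysis section lists new bone scan lesions and new symptoms as separate manifestations of progression. That describes the disease; it is not a rule for classifying a scan.

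**Where the category is used**
- The primary comparison in the Biostatistical analysis section rests on relative change in PSA and on adverse events. The sample size is built on those two. The bone scan appears in neither.
- The Data analysis section plans no bone scan proportion, test or comparison of arms.
- Time to progression runs to *PD*. The rule carrying that label in the Activity section is the PSA rule of three consecutive rises. The bone scan category is labelled progression (non-response). The placement of the time-to-progression text under the bone scan suggests a link, but the plan does not state one.

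**The case against.** The strongest defence is that nobody would apply the 'or' literally. Two negatives joined by 'or' are ordinary loose drafting for 'neither new lesions nor new pain', and the next line calls new uptake progression. In addition, 'requires' may state a necessary condition rather than a sufficient one, so a painless patient with new lesions is not forced into *stable*. Much of this stands: the double classification is the less likely outcome in practice. It does not rescue the rule. If 'requires' is only necessary, no sufficient definition of *stable* exists. If 'and' was meant, the pain-only patient still has no category, and placing him under *worse* relies on a term the plan leaves empty.

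It is also fair to say that pain is not foreign to the plan's idea of progression, since the Biostatistical analysis section lists new symptoms. So the documents do not show which reading was intended, and a sponsor who wants pain to count can keep it.

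A reader might infer four stronger things, which the documents do not support:

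- *Many patients are affected, and wrongly classified.* No frequency is given. Eligibility rests on rising PSA, the pain clause needs a site already seen on scan, and active pain requiring chronic opioids is excluded. The affected patients receive two categories or none, which is not the same as a wrong one.
- *One patient moves a planned result by 1/12 = 8.3 percentage points.* That is only the share of one man in a 12-patient arm; no bone scan comparison is planned. Follow-up imaging is due 5 and 17 weeks after completion of therapy. For Arm 1, vaccinated through week 7, the first is at about week 7 + 5 = 12, after the placebo-controlled period has ended. (Exact dates in the Schedule of Events table cannot be seen here.)
- *Unblinded staff decide the scan category.* The Study Design section does say "Study participants in Arm 2, but not the investigator, study personnel, or those study participants in Arm 1 will be blinded". But imaging is to be read by a professional radiologist, whose blinding is not described, and all patients learn their arm at week 8. The open design does not create this problem.
- *The bone scan is a primary endpoint, because the paragraph uses that word.* There it means the main way of reading this scan; the same section ranks the bone scan as secondary.

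**Conclusion.** The definitions are wrong as written, and the error is minor. Of the four combinations of new lesion and new pain, one falls in both categories under the written 'or', and a different one falls in neither under 'and'. Nothing else in the plan resolves either case.

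The conclusion assumes that 'new lesions' and 'new areas of uptake' denote the same finding. It does not depend on any numerical design input. An effect on time to progression is conditional on bone scan progression counting as PD, which remains open.

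**What to change.** Reconcile the two definitions so that each scan falls in exactly one category. Either route does this.

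1. **Scan only (simplest).** *Stable or improved*: no new focal uptake compared with baseline. *Progression*: one or more new areas of focal uptake. The first two rows of the table become stable and the last two progression. Record new bone pain, of any grade, as its own item on the case report form. This item is needed because the On-study evaluations section otherwise requires only Grade 2 or higher symptoms after baseline, or those leading to a change in treatment, so Grade 1 bone pain could go unrecorded.
2. **Pain counts, if that is the sponsor's intention.** Replace 'or' with 'and' in the stable definition, and add new pain at a previously seen site explicitly to the *worse or progression* side. The first row is then stable and the other three are not.

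It would help to say at the same time whether bone scan progression counts as PD for time to progression.

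The cost is a sentence or two of protocol wording and, under route 1, one case report form item; no procedure is added. The downside of route 1 is that pain without a new lesion no longer bars a scan from being called stable. The downside of route 2 is that a patient-reported symptom stays inside an outcome that was simplified to limit subjectivity.
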